### **11.2 Efficacy Analyses**

#### **11.2.1 Primary Efficacy Endpoint**

The objective of the *primary efficacy endpoint* analysis is to demonstrate through a formal hypothesis test that treatment with 16 weeks of sildenafil provides greater improvement in six-minute walk (6MW) distance than does placebo in subjects with sickle cell disease and PH.

The primary efficacy endpoint for the main study is the change in 6MW distance across 16 weeks of therapy. Missing values will be imputed based on the procedure detailed in section 11.5.5. In essence, the imputation methodology is a combination of Last Observation Carried Forward (LOCF) and the imputation of worst value observed or worst measurable value, depending on reason for discontinuation and on the availability of an assessment at the time of discontinuation. LOCF will be used to impute data for 1) subjects who are lost-to-follow-up and 2) subjects who prematurely withdraw from the randomized-double blind phase (for any reason) but complete the 6MW at the time of discontinuation. On the other hand, if a subject dies, the 6MW distance at 16 weeks will be set to zero meters. Finally, if a subject discontinues due to clinical deterioration, then the lowest observed 6MW value within that subject's treatment group and TRV stratum will be imputed as the 16 week value (see section 11.5.5 for additional details on imputation.)

The primary efficacy analysis is an Analysis of Covariance Analysis (ANCOVA) on 6MW distance change from baseline to Week 16 on the ITT Population. The primary

hypothesis test will be based on a test that the average change differs between the two treatment groups, with baseline 6MW distance and TRV stratum used as covariates. This type of model controls for any impact of baseline 6MW on the treatment effect without assumptions about the slope of the relationship between the baseline and Week 16 measures.

Secondary analyses of the primary efficacy endpoint are intended to demonstrate that the primary analysis results are robust. Analyses include:

- Replication of the analyses described above on the PP population
- A single two-sample Wilcoxon rank-sum test (the nonparametric alternative to the two-sample t-test) to compare the change from baseline to Week 16 in the sildenafil arm to the change from baseline to Week 16 in the placebo arm for the 6MW distance. For those subjects with missing Week 16 measurements, these measurements will be imputed using a last observation carried forward (LOCF) approach or by using the last possible measurement (see section 11.5.5).
- An Analysis of Variance (ANOVA) model which is a small deviation from the t-test approach and the ANCOVA model. This method will use the change from baseline to Week 16 with missing values imputed by LOCF or by using the last possible measurement (see section 11.5.5), as the primary endpoint. The analysis will be based on a cell-mean model with the four treatment-by-TRV-strata groups as the cells. The primary hypothesis will be based on a test that the average change across the two strata differs between the two treatment groups. The hypothesis will be tested with an F-test with 1 numerator and N-4 denominator degrees of freedom, where N is the number of subjects in the ITT population.
- A linear mixed model, which will incorporate the 6MW measurements from the baseline, Week 6, Week 10, and Week 16 assessments. This model allows for comparison of the 6MW distance over the two treatment groups, controlling for time, TRV stratum, and baseline 6MW distance as fixed effects and subject as a random effect. This analysis uses likelihood-based estimation, and subject-specific effects and correlations between the repeated measurements are modeled via the within-subject error correlation structure. All available data will be used to compensate for the data missing on a particular subject.

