These data are consistent with the results of an NIH pulmonary hypertension screening study. 195 adult patients with sickle cell disease were recruited from the greater Washington, DC region. All patients were screened with transthoracic echocardiograms and the tricuspid regurgitant jet velocity (TRV) was used to estimate the pulmonary artery systolic pressure. Pulmonary hypertension was prospectively defined by a TRV  $\geq$  2.5 m/s and moderate-to-severe PH defined by a TRV  $\geq$  3.0 m/s. Right heart catheterization was performed in consenting patients with TRV  $\geq$  2.8 m/s. This study revealed that 32% of patients with SCD had elevated pulmonary artery systolic pressure (TRV  $\geq$  2.5 m/s) and 9% had at least moderately elevated pressures (TRV  $\geq$  3.0 m/s). Multiple logistic regression analysis identified a history of renal or cardiovascular complications, increased systemic systolic blood pressure, markers of hemolysis (LDH), elevated alkaline phosphatase, and low transferrin levels as independent predictors of PH. Most importantly, TRV of at least 2.5 m/s, as compared to a velocity  $<$  2.5 m/s, was associated with an increased risk of death (RR 10.1; 95% CI, 2.2-47;  $P < 0.001$ ) and remained so after adjustment for other possible risk-factors in proportional hazards regression analysis. The 18 month mortality approached 20% for patients with a TRV  $\geq$  2.5 m/s. In another recent prospective study of 60 patients systematically sampled at a comprehensive sickle cell treatment center, the prevalence of PH (defined by an age and body-mass index adjusted nomogram) was 30 %. Further updated follow-up data from our cohort continues to demonstrate that PH is a strong independent risk factor for mortality with 45-month mortality rate of approximately 40 %. From Cox regression analysis the estimated risk ratio of death, relative to patients with TRV  $<$  2.5 m/s, was 4.4 (95% CI 1.6 to 12.2;  $P < 0.001$ ) for patients with TRV 2.5 to  $<$  3.0 m/s and 10.6 (95% CI 3.3 to 33.6;  $P < 0.001$ ) for patients with TRV  $>$  3.0 m/s. In addition, a study by De Castro and colleagues presented at the meeting of the American Society of Hematology reported a similar prevalence of PH and a remarkably similar 17% mortality rate for patients with PH over 2 years compared with approximately 2% for subjects without pulmonary hypertension. Ataga and colleagues have also shown a 10% mortality rate for patients with PH over 26 months in comparison to 1% in those patients without PH. Taken together, the retrospective and prospective studies strongly support the contention that PH is the greatest risk factor facing the aging population of patients with sickle cell disease and likely patients with other chronic hemolytic disorders.

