### 11.5.3 Multiple Comparisons and Multiplicity

The primary formal hypothesis test will be conducted using an alpha on a two-sided test of 0.05. Because only a single hypothesis test will be tested and other reported p-values will be considered descriptive, no adjustment for multiple comparisons will be made. Informal hypothesis tests conducted as a part of secondary analyses will all be two-sided tests, and the p-values from these tests will be presented as descriptive measures of strength of evidence. These descriptive p-values will be presented for differences between treatment groups in summary tables for secondary exploratory analyses.

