## 11.6 Sample Size

This study will randomize 132 subjects (66 to sildenafil and 66 to placebo). Sample size was determined based on the following considerations.

The measurement of primary interest is the change in 6MW distance from baseline to week 16. To estimate the trial sample size for the primary endpoint, we used data from Ghofrani's evaluation of the effects of sildenafil in subjects with chronic thromboembolic pulmonary hypertension. Ghofrani's study showed an average change from baseline of 53.7m in 6MW distance with a standard deviation of 67m after approximately 6 months of sildenafil treatment.

A t-test was used to compare the difference in change from baseline 6MW distance between the sildenafil and placebo treatment groups. In order to calculate the sample size the following assumptions were made:

- No subjects discontinue because of clinical worsening or death
- No subjects dropout prior to week 10 for other reasons
- Sixteen-week change in 6MW distance is normally distributed in both treatment groups
- Sixteen-week change in 6MW distance is 40m in subjects on sildenafil and there is no change in subjects on placebo (i.e., a difference of 40m between the two treatment groups)
- Standard deviation of change from baseline between 62 and 72m for the 16-week change in each of the treatment groups
- Power ranges from 80% to 90%
- Two-sided t-test with  $\alpha=0.05$

Table 6 presents the number of subjects needed per treatment arm for the range of assumed standard deviations and powers, thus the total number is 2 times the numbers presented in each cell.

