**Table 6. Sample size needed per treatment arm by assumed standard deviation and power**

| Change from baseline (6MW) | Standard deviation (m) | Power 90% | Power 85% | Power 80% |
|----------------------------|------------------------|-----------|-----------|-----------|
| Mean 40m                   | 62                     | 52        | 45        | 39        |
|                            | 67                     | 60        | 52        | 46        |
|                            | 72                     | 70        | 60        | 52        |

If we choose the standard deviation of change from baseline determined in Ghofrani's study (67m) and a power of 90%, then we would need 60 subjects enrolled per treatment

arm. If the standard deviation were to be larger (e.g. 72m), 60 subjects per treatment arm would still result in 85% power to detect a 40m change in 6MW distance in subjects treated with sildenafil versus 0m change in placebo treated subjects. We anticipate that up to 10% of the subjects may dropout during the randomization phase prior to week 10. In order to maintain study power in the presence of potential study dropouts, we will supplement the computed sample size with an additional 10%. Based on these data, we will randomize 132 subjects into the study (approximately 33 per each of four treatment arm/TRV strata combinations).

The data presented above were also used to develop power calculations under multiple scenarios.

- I. Using the two-sample t-test approach, power estimates were developed with the following assumptions
    - a) 5% of subjects randomized to placebo and 2.5% of subjects randomized to sildenafil will discontinue study medication due to clinical worsening or death, and therefore will have assigned values less than the smallest change in 6MW distance in a subject who completes the study. If 6MW is normally distributed in subjects who complete the study, simulations indicated that the power is still 90%.
    - b) The same result was obtained for percentages discontinuing study medication of 10% and 5% in placebo and sildenafil subjects, respectively.

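### The "simulations indicated that the power is still 90"% statement in section 11.6 does not cover the rule that scores a death as 0 m in the primary ANCOVA; under that rule power is lower whenever a material share of events are deaths

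*Protocol*

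**What the plan says.** **Scoring and test.** Section 11.2.1 makes the primary analysis an ANCOVA on change in six-minute walk (6MW) distance, with baseline 6MW and TRV stratum as covariates. For deaths, "if a subject dies, the 6MW distance at 16 weeks will be set to zero meters". Section 11.5.5 repeats the 0 m score. It gives subjects who stop for clinical worsening, without an end-of-study walk, the worst value from their own arm and stratum. A rank test is planned only as a robustness analysis: "A single two-sample Wilcoxon rank-sum test (the nonparametric alternative to the two-sample t-test"). Section 11.5.3 fixes the error rate: "The primary formal hypothesis test will be conducted using an alpha on a two-sided test of 0.05".

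**Sizing.** Section 11.6 assumes "a difference of 40m between the two treatment groups" and takes its SD from a small sildenafil study "with a standard deviation of 67m after approximately 6 months of sildenafil treatment". The basic calculation assumes that nobody stops for worsening or death. It gives 60 per arm for 90% power, raised by 10% to 66.

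**Scenario I.** Section 11.6 then lets 5% of placebo and 2.5% of sildenafil subjects stop for worsening or death, and they "will have assigned values less than the smallest change in 6MW distance in a subject who completes the study". With those values, "simulations indicated that the power is still 90"%. The same result is reported for 10% and 5%.

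**The concern.** Eligibility requires a baseline walk of 150-500 m, so a death enters the model as a change of -150 to -500 m. Against a planning SD of 67 m that is 150/67 = 2.2 to 500/67 = 7.5 SDs below zero. At a baseline of 350 m, one death among 66 moves an arm mean by 350/66 = 5.3 m on placebo, or (350+40)/66 = 5.9 m on sildenafil if the subject would otherwise have gained 40 m. It also inflates the residual variance.

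Scenario I is the only place where the protocol checks power against worsening or death, and its description of the assigned values does not mention 0 m. If the 90% belongs to milder values than the primary analysis will use, the sponsor and the DSMB are relying on power that the trial may not have. Deaths are foreseeable from the protocol's own background: section 2.1 reports that "The 18 month mortality approached 20% for patients with a TRV" of at least 2.5 m/s.

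**Working it through.** **Inputs from the protocol.** Two-sided alpha 0.05; effect 40 m; SD 67 m; 66 per arm; event rates (placebo/sildenafil) 5%/2.5% and 10%/5%; death = 0 m; baseline 150-500 m.

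**Assumed, not in the protocol.** Baseline walk normal with mean 350 m (range tried 300-400 m) and SD 90 m, truncated to 150-500 m. Change in survivors is unrelated to baseline. Each simulated setting used 4,000 to 10,000 trials. Ranges below span event-rate scenarios and repeated simulations.

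**1. Table 6.** n = 2 × 67² × (1.960 + 1.282)² / 40² ≈ 59 per arm; the exact t calculation gives 59.94, so 60, as stated. Exact power at SD 67 m is 90.0% with 60 per arm and 92.6% with 66.

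**2. Scenario I on its own terms.** With events just below the smallest completer change, 66 per arm gives about 91% (5%/2.5%) and 90% (10%/5%). With 60 per arm it gives about 89% and 87-88%. The stated 90% therefore reproduces at 66 per arm.

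**3. Scenario I under the written rules.** Deaths at 0 m, worsening at the lowest observed walk in the arm and stratum, ANCOVA, 66 per arm, mean baseline about 350 m:

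| Share of events that are deaths | Power, both event-rate scenarios |
|---|---|
| none | about 88-91% |
| half | about 82-86% |
| all | about 77-83% |

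**4. Mortality implied by section 2.1.** At constant hazard, 16-week risk = 1 - (1 - m)^(3.68/months), since 16 weeks is 16/4.345 = 3.68 months.

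- 20% at 18 months: 4.5%, or 2.9 deaths per 66
- 17% at 2 years: 2.8%, or 1.9 deaths per 66
- 10% at 26 months: 1.5%, or 1.0 death per 66

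**5. Power with deaths at 0 m, 66 per arm.**

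| Placebo mortality | ANCOVA, equal in both arms | Equal, baseline mean 300-400 m | ANCOVA, sildenafil half of placebo |
|---|---|---|---|
| 1.5% | 79% | 77-82% | about 88% |
| 3% | 68% | 64-72% | about 84-86% |
| 4.5% | 58% | 55-63% | about 82% |

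Analytic check for equal mortality p = 3/66 = 0.0455 and mean baseline 350 m:

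- Sildenafil variance: 0.9545 × 67² + 0.0434 × 390² ≈ 10,880
- Placebo variance: 0.9545 × 67² + 0.0434 × 350² ≈ 9,600
- Pooled SD ≈ 101 m, against 67 m without deaths
- Mean difference: 40 × 0.9545 = 38.2 m; standard error: 101.2 × √(2/66) = 17.6 m
- Power ≈ Φ(38.2/17.6 - 1.96) ≈ 58%

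**6. Dependence on the split.** Fixed deaths, sildenafil/placebo: 1/1 gives about 84%, 1/2 about 89%, 0/1 about 95%, 1/0 about 76% and 2/0 about 51%.

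**7. Comparison and error rate.** An unstratified Wilcoxon test has about 85-92% power across the random-event settings in steps 3 and 5. Without deaths it has about 91%, against 92-93% for ANCOVA. With equal deaths at 0 m and no drug effect, ANCOVA type I error is 4.5-5.5%.

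**The case against.** **The 90% claim is not shown to be false.** This stands. Section 11.6 says only that the assigned values lie below the smallest completer change. It does not say by how much, and it pools worsening with death. A reader might infer that the simulation was done wrongly, but on its own scoring the 90% reproduces. What can be said is narrower: values just below the worst completer give the stated figure but are not the death rule, while 0 m for a material share of events gives less than 90%.

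**The steepest losses need equal mortality.** This also stands. A reader might infer that one to three deaths in each arm always cut power to 79-58%. Those figures are averages over random deaths at equal rates. Exactly one death in each arm gives about 84%, and the protocol's own assumption of twice as many events on placebo gives about 88-82%.

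**Mortality may be overstated.** The rates come from observational cohorts and assume constant hazard. The trial excludes unstable conditions and requires that the investigator expect the subject to complete 16 weeks.

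**No validity error.** A reader might infer that a chance imbalance of deaths raises the false-positive rate. It does not, because the residual SD rises as well and type I error stays near 5%.

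**Partly handled already.** Scoring death as the worst value is deliberate and prespecified, and the Wilcoxon test and a mixed model are planned as robustness analyses. These do not restore the power of the single confirmatory test. It is also true that most Scenario I results in step 3 fall within the 80-90% range considered in Table 6, but section 11.6 states 90%, not that range.

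**Conclusion.** The point holds as a mismatch between the stated power and the scoring rule. The 90% in section 11.6 is not established for the analysis in sections 11.2.1 and 11.5.5. At the protocol's own event rates, power stays near 90% only if few events are deaths; otherwise it falls to the low 80s or high 70s. Equal mortality at the cited cohort rates would take it lower, to about 58% at the upper end.

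These sizes rest on an assumed baseline distribution, an assumed share of deaths and, for the cohort-based figures, constant hazard. The direction does not depend on the baseline mean over 300-400 m. With so few deaths expected, the achieved power turns largely on how one or two of them split between the arms.

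The documents do not support the stronger conclusion that the primary ANCOVA is invalid or must be replaced. The section 11.6 statement should be corrected; the choice of test is a matter of judgement.

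**What to change.** **Needed.** In section 11.6, re-run Scenario I with the primary ANCOVA, deaths at 0 m and worsening scored as in section 11.5.5. State the number per arm, the assumed share of deaths and the assumed baseline mean, and include an equal-mortality case. Replace the single 90% with the resulting range. The cost is one simulation and a paragraph of text.

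**Optional, before unblinding.** Consider a rank-based primary test, for example a Wilcoxon test stratified by TRV with deaths ranked lowest, and keep the ANCOVA in metres as supportive. The power quoted above is for the unstratified test, so the stratified version should be simulated before it is adopted. The cost is about 1-2 points of power if nobody dies, and the effect in metres would no longer be the primary result.

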### 11.5.5 Handling of Dropouts and Missing Data

Investigators should make every effort to obtain end of study assessments when subjects discontinue from the study due to clinical deterioration.

For the ANOVA, ANCOVA, and the Wilcoxon rank sum test, missing data at the Week 16 assessment will be derived from predefined replacement rules:

- *Last Observation Carried Forward (LOCF)*. Subjects without an assessment at Week 16 due to missing data (e.g. lost to follow-up) will have their last 6MW distance, Borg dyspnea index, and WHO functional classes carried forward (LOCF). Additionally, LOCF will be used for those who discontinue early for any reason, but who participate in a study assessment at the time of withdrawal.
- *Worst measurable value and worst observed value*. A subject who is missing endpoint values at 16 weeks because of discontinuation of study medication due to clinical worsening or death will be assigned values equal to or worse than the worst values recorded in a subject who does not discontinue study medication. Subjects who die will be assigned the worst value possible based on the scale of the endpoint (e.g., 0m for the 6MW, 10 for the Borg dyspnea and FC IV), whereas subjects who discontinue due to clinical worsening and who also do not participate in an end of study assessment of that endpoint will be assigned the worst value from that subject's treatment group and stratum.
- No hemodynamic parameters will be imputed.

No data imputation will be performed for the linear mixed model analyses, and no data will be discarded. For persons who withdrew from treatment early, this type of analyses

have been designed to use the data obtained to the point that they were lost. For these secondary analyses, missing data will be treated as randomly missing data.

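### Clinical-worsening dropouts with no final walk take the lowest distance of their own arm and TRV stratum: this conflicts with 11.5.5 and 11.6, modestly raises type I error, and credits sildenafil failures with the drug effect

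*Protocol*

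**What the plan says.** Three places in the Protocol set or assume a value for a subject who stops because of clinical worsening.

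- **Section 11.2.1** (primary analysis): the lowest observed walk in the subject's "treatment group and TRV stratum will be imputed as the 16 week value". This is a distance from one arm-by-stratum cell. The analysed quantity is change from baseline, in an ANCOVA with baseline distance and TRV stratum as covariates.
- **Section 11.5.5**: as a general principle, subjects missing Week 16 because of worsening or death "will be assigned values equal to or worse than the worst values recorded in a subject who does not discontinue study medication". The next sentence gives deaths the worst possible score (0 m for the walk). It gives worsening subjects without an end-of-study assessment the worst value of their own treatment group and stratum. Anyone assessed at withdrawal has that value carried forward.
- **Section 11.6, scenario I(a)** (power): such subjects "will have assigned values less than the smallest change in 6MW distance in a subject who completes the study". This is on the change scale and not tied to an arm.

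The Wilcoxon and ANOVA bullets in 11.2.1 name a further fallback, a last possible measurement, which 11.5.5 does not define.

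**The concern.** The rule feeds the only formal hypothesis test, and three features of it are awkward.

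1. The penalty is set on the distance scale and the endpoint is change. Nothing ties the imputed distance to the subject's own baseline.
2. The minimum comes from one cell. Every failure in that cell gets the same random number, and the ANCOVA treats these as separate observations.
3. The minimum is arm-specific. If the drug lifts completers' distances it lifts the sildenafil minimum too, so a sildenafil failure is scored better than a placebo failure for no reason of its own.

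At stake are the nominal 5% error rate, the meaning of the estimate when treatment fails, and whether the power scenarios describe the analysis that will be run.

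**Working it through.** **Inputs from the Protocol.** Section 11.5.3: "The primary formal hypothesis test will be conducted using an alpha on a two-sided test of 0.05". Section 11.6: "a difference of 40m between the two treatment groups"; a cited study "with a standard deviation of 67m after approximately 6 months of sildenafil treatment"; "This study will randomize 132 subjects (66 to sildenafil and 66 to placebo". That is 132/4 = 33 per arm-by-stratum cell. Section 5.3.3: baseline walk 150–500 m. Scenario I failure rates (worsening or death): 5% placebo and 2.5% sildenafil, or 10% and 5%.

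**Assumptions not in the Protocol.** Baseline about normal with mean 350 m and SD 85 m (80 m in some runs), truncated to 150–500 m; failures at random unless stated; equal failure rates under the null; deaths not modelled separately. The failure rates below count only subjects with no walk at withdrawal.

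**Step 1: the plan's own figures.** The protocol states "a power of 90%, then we would need 60 subjects enrolled per treatment" arm. The noncentrality is 40 / (67 × √(2/60)) = 3.27 on 118 df, which gives 90% power. Then 60 × 1.1 = 66 per arm, 132 in total. Simulating scenario I with its own rule gives 89.2% and 88.5% at 60 per arm, and 92.0% and 91.6% at 66 per arm. The stated figures reproduce.

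**Step 2: the rules side by side.**

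| Place | Scale | Reference group |
|---|---|---|
| 11.2.1, and the specific sentence in 11.5.5 | distance | own arm and stratum |
| 11.5.5, general principle | not stated | any subject who stays on drug |
| 11.6, scenario I | change | any completer |

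An own-cell minimum breaks the general principle whenever another cell holds a lower value. With a 40 m effect, the mean imputed distance is about 183 m on sildenafil and 145 m on placebo.

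**Step 3: type I error.** Planned ANCOVA, no drug effect, 8,000–20,000 simulated trials per main setting (simulation error about 0.15–0.25 points).

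| Unassessed failures per arm | Own-cell minimum | One common worst change |
|---|---|---|
| 2.5% | 5.3–5.5% | 4.8–5.5% across the three rows |
| 5% | about 6% | |
| 10% | 6.4–7.5% | |

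Other baseline distributions, a baseline slope of −0.3, or a change SD of 40 m give 5.6–6.2% at 5% failing and 6.6–7.8% at 10%. The excess is symmetric. In one null variant at 5% failing, 5.87% of trials rejected and 2.94% rejected in favour of sildenafil. A common worst value is noisy too, but the noise is the same in both arms and cancels in the comparison.

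**Step 4: the estimate when the drug works.** With a 40 m completer effect, failures are imputed at about −201 m (placebo) and −163 m (sildenafil), a gap of 38 m. If a fraction f fails in each arm, the expected estimate is (1 − f) × 40 + f × gap.

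- f = 10%, own-cell rule: 0.90 × 40 + 0.10 × 38 = 39.8 m (simulated 39.8 m).
- f = 10%, common value: 0.90 × 40 + 0 = 36.0 m (simulated 35.6–35.9 m).
- f = 5%: 39.9 m against 38.0 m.

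**Step 5: failures scored as improved.** If only Week 16 or completer walks count as observed, about 1–2% of imputed subjects get a positive change under random failure, and 4–6% when failures have low baselines. If baseline walks also count, none can. Type I error is then still 5.7% at 5% failing and 6.5% at 10%.

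**Step 6: power under the planned rule.** At scenario I rates with 66 per arm it is about 89–90%, against roughly 90–92% with one common worst change.

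**The case against.** The strongest reply is that the rule reaches few subjects. A walk at withdrawal is carried forward. Section 7.1 asks for all end-of-study assessments at discontinuation and does not require stopping drug for PH deterioration. Section 11.5.5 presses investigators to obtain them. The rates in 11.6 cover worsening or death, before any carrying forward, and the highest is 10% on placebo with 5% on sildenafil. This stands: 10% unassessed in both arms exceeds anything the protocol plans for, and at 2.5% the inflation is barely separable from simulation noise.

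It can also be said that the two sentences in 11.5.5 are principle and detail, that 11.6 describes a power scenario and not an analysis rule, and that the mixed model uses no imputation. In part this stands, since an analyst would know to use the own-cell value. But that value does not satisfy the principle. The mixed model is secondary and assumes data missing at random, and the Wilcoxon test uses the same replacement rules as the ANCOVA.

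Three stronger readings are tempting and not supported:

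- **That the rule produces false positives for sildenafil.** With no drug effect the imputed values are equal on average in both arms (for example 141.7 m and 141.6 m).
- **That deteriorating patients will commonly count as improved.** It is rare, and impossible under one reading of the wording.
- **That the 90% power claim fails.** It was shown for another rule, but it survives under this one.

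**Conclusion.** The point holds in moderate form and should be fixed. The imputation for unassessed worsening is set on the wrong scale and from the subject's own cell. It conflicts with the general statement in 11.5.5 and differs from the rule simulated in 11.6.

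The two main consequences are separate. Under the null, the shared minimum adds up to half a point to a 5% test at 2.5% unassessed failures per arm, about one point at 5%, and 1.4–2.5 points at 10%. Under a 40 m effect, sildenafil failures receive about 38 m of credit, which removes a penalty of about 4 m at 10% failing in each arm. That is bias relative to an endpoint on which failure is equally bad in either arm, and it does not cause the type I inflation.

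The sizes rest on the assumed baseline distribution and failure mechanism. The direction of both effects does not depend on the baseline distributions and failure patterns tried.

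**What to change.** In 11.2.1 and 11.5.5, give every clinical-worsening dropout without an end-of-study walk one common **change** value: the smallest observed change to Week 16 among completers of both arms and both strata combined. Give each death the lower of that value and the change implied by 0 m. The lower-of clause matters because a death from a 150 m baseline implies only −150 m, which could rank above the common value. Both rules yield a number that an unranked ANCOVA can use.

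Apply the same rule in the Wilcoxon and ANOVA bullets, in place of the undefined fallback, and in the 11.6 scenarios. Make the change before unblinding.

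The cost is wording, with no loss of power in the protocol's scenarios. The estimate becomes smaller: about 36–38 m instead of 40 m at 5–10% balanced failures. The average penalty also becomes milder. In a check with a 40 m effect the common value averaged about −160 m (160/67 ≈ 2.4 SDs). At 10%/5% failing, the expected estimate is then 0.95 × 40 − 0.05 × 160 + 0.10 × 160 = 46 m, against 38 − 0.05 × 163 + 0.10 × 201 ≈ 50 m under the own-cell rule.
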